### Feasibility economic evaluation

A feasibility economic evaluation will be embedded within the feasibility cRCT; therefore, participants will provide consent to take part in this element of the study during recruitment to the feasibility cRCT. As this is a feasibility economic evaluation, we will not provide cost-benefit, effectiveness, or utility estimates. Instead, this part of the study aims to explore the feasibility of data collection for an economic evaluation within a definitive trial.

#### Data collection.

We will evaluate the feasibility of collecting data related to health and social resource use. Health and social care resource use will be captured using a modified Service Use Questionnaire adapted from previous Service Use logs administered to this population [34,41]. Participants will be asked to complete a retrospective questionnaire to report their healthcare experiences over the past month at baseline and at the 3-month follow-up [41]. This will capture information on care received through primary care, outpatient departments, emergency departments, inpatient hospitalisations, and mental health services. The EQ-5D-5L will be administered to participants at baseline and at three-month follow-up, alongside the clinical outcome questionnaires [42].

#### Data analysis.

Descriptive statistics of the response rates, missing data, and costs will be provided [43]. This descriptive approach is recommended for feasibility studies, as it provides an overview of the feasibility of the data collection methods without attributing causality to any observed differences in the data [43]. Costs will be estimated according to NHS reference costs and presented as a descriptive cost-consequence analysis. Missing data for the service use questionnaires and the EQ-5D-5L will be presented as frequencies to assess the feasibility of data collection in a future cRCT. The acceptability of using service-use questionnaires to collect healthcare-use data will also be explored in the qualitative process evaluation.

### Process evaluation

#### Participants.

Participants will include patients who have participated in the feasibility cRCT, their caregivers, and healthcare workers with experience of the BA intervention. We aim to recruit 15 patients who participated in the study, 10 healthcare workers who either delivered the intervention or had the opportunity to work alongside its delivery, and five carers of individuals who received the integrated BA intervention [44].

Healthcare workers will be eligible for participation in the study if:

They are a member of a multidisciplinary team, including nurses, medical doctors, healthcare support workers, physiotherapists, and social workers.They have had exposure to the intervention, either as a facilitator who delivered it or as a team member present in the unit during its delivery.They have at least three months of experience within the kidney care setting.

Carers will be eligible for participation in the study if:

They are a family member or friend who provides support to a participant in the study who received the integrated BA intervention.They are over 18.They have the capacity to provide informed consent.

We will recruit patients from both the intervention and control groups to assess the acceptability of the intervention and trial procedures.

#### Recruitment.

Patients recruited into the feasibility cRCT will have the opportunity to participate in the qualitative process evaluation. They will be provided with a further participant information sheet providing an overview of the qualitative process evaluation, which will have been developed in collaboration with our PPI panel. Consent will be obtained before the interview begins. We will attempt to recruit a diverse range of patient participants at the two sites to ensure that the interviews capture a broad spectrum of experiences across demographic groups.

Healthcare workers who have delivered the BA intervention or were on shift when it was delivered will be approached directly by a researcher and invited to participate in the process evaluation. They will receive a participant information sheet and will be given at least 24 hours to decide whether they wish to participate.

Carers will be recruited through patients who received the BA intervention as part of the feasibility cRCT. Participants who received the intervention will be provided with a recruitment pack to provide to a family member or friend. All participant-facing materials will be developed in collaboration with our PPI panel.

#### Data collection.

We aim to conduct 35 semi-structured interviews, comprising 15 with participants who have taken part in the study, 15 with healthcare workers with experience of the intervention (including intervention facilitators), and 5 with carers of participants who received the intervention. Semi-structured interviews will enable an in-depth exploration of experiences within the feasibility cRCT and allow data collection to align with healthcare workers’ work commitments and patients’ treatment burden. Interviews will be conducted in a suitable location for participants. In previous feasibility studies conducted in haemodialysis units, this is frequently during the workday or during haemodialysis treatment [45].

The semi-structured interviews will follow a topic guide structured around the theoretical framework of acceptability [46]. They will focus on the acceptability of the integrated BA intervention and the trial procedures (including screening with the PHQ-4). These interview guides will be informed, developed, and refined through consultation with the PPI panel. The interviews will be audio-recorded and transcribed verbatim.

#### Data analysis.

Interviews will be recorded verbatim using encrypted recording devices. Thematic analysis will be conducted, using NVivo, to identify overarching themes in the data. The interviews will be coded line by line, and these codes will then be reviewed to group relevant codes. These groups will then be iteratively revised to identify the common themes and sub-themes in the data [47]. We will present the themes to our PPI panel to explore their perspectives on the findings, how they can inform a definitive trial, and their relevance to practice.

### Progression criteria

Progression to a definitive cRCT will be determined by recruitment rates and the acceptability of the methods and intervention for patients and staff. Both quantitative and qualitative data will be used to determine the feasibility of a cRCT [34,48]:

Recruitment75-100% of the target sample size recruited across the two sites will result in progression to a definitive trial.50-74% of the target sample size recruited across the two sites will result in progression to a full trial, following appropriate amendments to address barriers to recruitment.25-50% of the target sample size recruited across the two sites will result in progression to a pilot study following review by the study steering committee and future co-applicants to ensure that adequate revisions are made to address barriers to recruitment.<25% of the target sample size recruited will result in the study not progressing to a full trial.RandomisationEvidence of substantial or consistent contamination from the method of clustering (either due to high rates of contamination or evidence of significant contamination from qualitative interviews) will result in a review of the randomisation and clustering method, before progression to a definitive trial.InterventionProgression to a full trial will be contingent on the acceptability of the integrated BA intervention for both patients and healthcare professionals. This will be determined by exploration within the qualitative process evaluation. Any necessary modifications or adaptations will be made in collaboration with our PPI panel.Data collectionThe use of the clinical outcome measures in a future trial will depend on their acceptability, determined by the proportion of missing information, and through the qualitative process evaluation.

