#### Sample size.

As this is a feasibility study, a power calculation was not conducted, as we are not looking to measure effectiveness. There is no consensus on the appropriate sample size for a feasibility study [32,33]. However, a total sample size of 52 people would allow us to estimate the recruitment rate with a precision of ±9% (assuming a previously observed 40% recruitment rate and a 95% confidence interval). This provides an appropriate level of precision to inform the likely number of people the full-scale trial might need to screen. Given that we have four clusters, this would also allow for a minimum of 12 participants per cluster, with a total of 26 participants recruited from each site [34].

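### Two recruitment progression bands both include 50% of target, so exactly 26 of 52 recruits meets two different pre-specified outcomes

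*Protocol article*

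**What the plan says.** The Progression criteria section gives four recruitment bands, each tied to an outcome and expressed as a share of the target recruited over both sites together:

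- 75% to 100%: a definitive trial.
- The second band: "50-74% of the target sample size recruited across the two sites will result in progression to a full trial, following appropriate amendments". The amendments are meant to deal with barriers to recruitment.
- The third band: "25-50% of the target sample size recruited across the two sites will result in progression to a pilot study following review". That review falls to the steering committee and future co-applicants, and is to ensure adequate revisions.
- The lowest band: "<25% of the target sample size recruited will result in the study not progressing to a full trial".

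The target comes from the Sample size section, which says that "a total sample size of 52 people would allow us to estimate the recruitment rate with a precision of ±9"%. The basis for this figure is stated as "assuming a previously observed 40% recruitment rate and a 95% confidence interval". The split between the sites is given at the end of the same section: "with a total of 26 participants recruited from each site". The section on progression does not say which band applies when a result meets two of them.

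**The concern.** A progression rule fixed in advance is meant to map each possible result to one outcome, so that the choice is not made with the result in view. Here 50% is the lower limit of one band and the upper limit of the next. Because the target is an even number, 50% is a count that can occur.

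The two outcomes differ. One leads to a full trial after amendments, the other to a further pilot study. The formal review is attached only to the pilot band, so at exactly half the target the text does not settle whether that review is required. Recruitment is also the only progression criterion with numerical thresholds. Contamination, acceptability of the intervention and missing outcome data are judged without them.

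**Working it through.** **Inputs.** Target N = 52, with 26 at each of two sites (2 × 26 = 52), a 40% recruitment rate and a 95% interval, all from the Sample size section. The band limits come from the Progression criteria section.

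**The plan's own figure.** Reading 52 as the number who consent, the number of eligible people approached is 52 / 0.40 = 130. The half-width of the 95% interval is then 1.96 × √(0.40 × 0.60 / 130) = 8.4% by the plain normal formula. It is 8.8% with the continuity correction (adding 1/260) and 8.7% by the exact interval. The last two round to the stated ±9%. The target therefore stands as the denominator of the bands, and the point here does not depend on the precision figure.

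**The bands in whole participants.** Each count k from 0 to 52 was converted to 100 × k / 52 and compared with the four bands as written. The counts around the edges are:

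| Recruited | Share of 52 | Band or bands met |
|---|---|---|
| 12 | 23.08% | no progression |
| 13 | 25.00% | pilot after review |
| 25 | 48.08% | pilot after review |
| **26** | **50.00%** | **pilot after review and full trial after amendments** |
| 27 | 51.92% | full trial after amendments |
| 38 | 73.08% | full trial after amendments |
| 39 | 75.00% | definitive trial |

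Only 26 falls in two bands, and no count falls in none. Rounding the shares to whole percentages gives the same result. The apparent gap between 74% and 75% contains no attainable count, because 38 is 73.08% and 39 is 75.00%.

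**After the change.** With the third band ending at 49%, the counts divide into 0–12, 13–25, 26–38 and 39–52, and each count falls in exactly one band. The new nominal gap between 49% and 50% is also empty, because 25 is 48.08% and 26 is 50.00%.

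**The case against.** The strongest reply is that this is an editorial slip whose intention can be read from the rest of the list. The band below 75% stops at 74%, and the lowest band is strictly below 25%, so at both other edges the boundary value goes to the higher band. On that pattern 50% belongs with the full trial after amendments. The argument is a good one and it supports the proposed fix. It remains an inference, because the text does not state it.

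The second reply is that the reach is small, and that is right. One count in 53 is affected. As an illustration, assume that 130 eligible people are approached and each consents independently. The chance of exactly 26 consenting is negligible at the protocol's 40% rate. It is about 9% at a true rate of 20%, the value that makes 26 most likely.

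A reader might go further and infer that the study's go/no-go decision is contradictory, or that the overlap leaves the decision to be picked at will once the data are in. The document supports neither. The stop boundary at 25% and the unamended-progression boundary at 75% are both clean, and the two bands that meet at 50% both continue the programme with revisions to address recruitment. The section also says that acceptability and qualitative data enter the decision, so the count was never the sole determinant and some judgement after the data is built in. None of that resolves the tie: each band states its own outcome, and nothing says that the qualitative findings choose between two bands.

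It might also be said that a journal article condenses the full protocol. That would excuse an omission, but here both limits are printed and they conflict.

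**Conclusion.** The point holds as a minor error in a decision threshold. At exactly 26 recruits the published rule prescribes two different next steps and gives no tie-break; at every other count from 0 to 52 it prescribes one. This rests on a target of 52 and on reading the printed limits as inclusive, which is how the ranges are written. It has no bearing on the sample size, the randomisation or any analysis.

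**What to change.** Make the 50% edge exclusive on one side. The change that matches the other edges is to end the lower of the two bands at 49% instead of 50%, which is 13 to 25 participants, so that 26 falls in the band for a full trial after amendments. Moving the lower limit of the upper band above 50% would also remove the overlap, but would put 26 in the pilot band. The document does not say which is meant, so the sponsor should confirm the intended split.

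The correction should be made before the recruitment result is known, since a later one could look as if it had been chosen to suit the result. It costs one number in one line and changes no procedure. The other boundaries can stay as they are.

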## Discussion

People with kidney failure receiving haemodialysis are at higher risk of developing mental health conditions, such as depression [3]; despite this, there is currently limited access to support and specialist mental health services. Alongside current barriers to accessing support, such as long waiting times, patients spend a significant portion of their week attending dialysis appointments [6,7]. One potential solution is to explore ways to improve access to mental health support and treatment within their existing treatment regimen.

While BA is a NICE-recommended treatment for depression in adults, including those with co-occurring long-term conditions [17], it has never been delivered or evaluated for patients with kidney failure during their routine haemodialysis appointments [10,49]. Therefore, our primary aim isn’t to explore its effectiveness, but rather to first assess the feasibility and acceptability of delivering BA during haemodialysis. We will explore this through various methods; firstly, a pilot cRCT to determine the feasibility of conducting a definitive cRCT to evaluate the BA intervention, secondly, a qualitative process evaluation to explore the acceptability of the intervention and methods, and finally, a feasibility economic evaluation to explore the best methods for evaluating cost-utility in a definitive trial.

A key strength of this study is that the intervention was adapted in close collaboration with patients and carers, with the aim of further refinement following delivery within the pilot cRCT. The protocol follows the Medical Research Council’s (MRC) guidance on the evaluation of complex interventions [27], using a comprehensive mixed-methods approach to explore feasibility and acceptability. While the study will involve only two sites in England and we do not have the resources to translate and culturally adapt the intervention, which limits the generalisability of the findings, we have deliberately selected sites that serve different demographics. Therefore, the feasibility study will provide us with an understanding to refine the protocol and intervention for a future definitive cRCT.
